### Hypothesis and data analysis

The primary hypotheses assert that brief interventions (CBT and healthy lifestyle) will prevent the development of psychological distress by improving psychological coping skills and healthy behaviours. A further hypothesis is that the intervention groups will show improved resilience and quality of life compared with the control group; however, we are not hypothesizing a significant difference between the treatment groups themselves.

The effectiveness of the interventions will be determined by conducting multivariate analyses of variance with repeated measures for revealing differences within and between groups, as well as reporting effect size changes. Potential confounding factors, such as pre-injury health and education, will be adjusted for in the analysis. Correlation analyses and multiple regression will also be used to analyse predictors of psychological distress over time. The intervention satisfaction questionnaire will be analyzed to assess participant satisfaction of the overall treatment approach. Clinically significant improvements or recovery will be determined by identifying the proportion of participants who demonstrate a significant reduction in their symptoms.

An interim analysis will re-evaluate the assumptions made for the study’s sample size calculation, with re-estimation made if required, unless the trial needs to be stopped as a result of significant and consistent indications of elevated psychological distress associated with the interventions, according to the safety measures and endpoint.

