### Sample size

Based on prior results of CBT and healthy lifestyle interventions [1, 4, 5], the two interventions are assumed to have at least a small to moderate mean effect size of 0.25 (Cohen’s *d*) when compared with the control group. Assuming an α probability of 0.05 and a power of 80 % for a three-group comparison analysis with four measures over time, a sample of 135 participants must be recruited to detect a true difference (see Fig. 1). It is therefore proposed to recruit at least 180 adult participants, randomly assigned to one of the three groups each with at least 60 participants per group. This is to accommodate for the loss to follow-up of approximately 25 % of participants, based on similar research [27].

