### Outcome measures

#### Primary and secondary measures

Table 3 shows the primary and secondary outcome measures. The primary outcome measure is the presence and severity of psychological distress or disorder across four time points assessed by a mixture of psychometric mental health measures and diagnostic interviews based on criteria of the fifth edition of the *Diagnostic and Statistical Manual of Mental Disorders* for depression, anxiety and post-traumatic stress disorder. Secondary outcome measures will include motor vehicle crash injury history, employment, social life, resilience and self-efficacy, as well as indicators of physical health and lifestyle.

**Table 3 Tab3:** Primary and secondary outcome measures acrossbaseline, post-treatment and follow-up

Measure	Primary	Secondary	Baseline	3 months	6 and 12 months
Demographics					
Sex, age, weight, height		×	×		
Marital status		×	×		
Highest level of education		×	×		
Motor vehicle crash history					
Motor vehicle crash date		×	×		
Driver or passenger		×	×		
Perception of danger during motor vehicle crash		×	×		
Hospital admission: yes or no		×	×		
Days spent in hospital		×	×		
Involvement of lawyer		×		×	
Referral to psychologist or psychiatrist		×		×	
Satisfaction with claims process: 3-point Likert scale		×			×
Claim finalization: yes or no		×			×
Employment					
Pre-motor vehicle crash employment: part-time, full-time, pensioner		×	×		
Modified hours since motor vehicle crash: yes or no		×	×	×	×
Returned to work: yes or no		×	×	×	×
Expectation of return to work: 11-point Likert scale		×	×	×	×
Reason for non-return to work		×	×	×	×
Number of days after motor vehicle crash for return to work		×	×	×	×
Social life					
Returned to activities after motor vehicle crash: yes or no		×	×	×	×
Expectation of return to pre-motor vehicle crash activities: 11-point Likert scale		×	×	×	×
Pre-motor vehicle crash social activity quality		×	×	×	×
Satisfaction of pre-motor vehicle crash social supports: 11-point Likert scale		×	×	×	×
Satisfaction of pre-motor vehicle crash social engagements		×	×	×	×
Expectation of return to pre-motor vehicle crash activities: 11-point Likert scale		×	×	×	×
Pre-motor vehicle crash relationship quality: 5-point Likert scale		×	×	×	×
Lifestyle habits					
Alcohol: Alcohol Use Disorders Identification Test	×		×	×	×
Smoker: yes, no, amount per day		×	×	×	×
Health					
Health Status: SF-12		×	×	×	×
Psychology or psychiatric history: yes or no		×	×	×	×

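### Repeated-measures MANOVA, the only named effectiveness test, uses complete four-visit records only, handles baseline inefficiently and does not suit the yes/no primary outcomes

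*Protocol article*

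**What the plan says.** All references are to the protocol article.

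- **Hypothesis and data analysis.** Effectiveness rests on "conducting multivariate analyses of variance with repeated measures for revealing differences within and between groups", with effect sizes reported. Regression serves another purpose: "Correlation analyses and multiple regression will also be used to analyse predictors of psychological distress over time". Clinical improvement is to be judged by "identifying the proportion of participants who demonstrate a significant reduction in their symptoms", with no group comparison attached. On covariates: "Potential confounding factors, such as pre-injury health and education, will be adjusted for in the analysis". The baseline score of the outcome is not among the examples.
- **Sample size.** The calculation is "for a three-group comparison analysis with four measures over time", with an alpha "probability of 0.05 and a power of 80" per cent. It needs 135 participants; 180 are recruited to "accommodate for the loss to follow-up of approximately 25" per cent.
- **Methods/design, opening paragraph.** Baseline is one of the four measurement points. A 12-month assessment of controls is stated only for those who do not want either programme. Under Interventions, controls are offered a programme after their 6-month assessment.
- **Primary and secondary measures, and Table 3.** The primary outcome covers both presence and severity of distress or disorder, from rating scales and "diagnostic interviews based on criteria of the fifth edition of the" diagnostic manual. Table 3 marks the diagnoses as primary, and also suicidal thoughts, recorded as yes or no.

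**The concern.** The named test does not fit the data the trial expects to collect, in three respects.

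1. **Incomplete participants.** Classical repeated-measures MANOVA needs the full outcome vector. Someone who misses only the 12-month visit contributes nothing, even at post-treatment. If distress drives drop-out differently across arms, the completers' contrast is biased. The control arm has an extra route to an incomplete record, because accepting a programme after month 6 leaves a control with no stated 12-month assessment.
2. **Baseline.** It enters as a fourth outcome, although treatment cannot have affected it. Its better use is to remove between-person variance.
3. **Binary primary outcomes.** The trial aims to prevent disorder from developing, so whether a diagnosis is present is central. MANOVA assumes roughly multivariate normal responses, and no method for binary data is named.

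At stake are avoidable bias and imprecision in the main comparison, and the lack of a suitable test for the diagnostic endpoints.

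**Working it through.** **The plan's own figure.** 135 / (1 − 0.25) = 180, and 180 × 0.75 = 135. The allowance for loss is correctly computed, so a 25 % loss does not by itself take a complete-case analysis below its target.

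**Number excluded.** 0.25 × 180 = 45. How many of these gave usable post-baseline data depends on when they left, which the article does not say. With an assumed cumulative loss of 8 / 17 / 25 % at the three visits, later leavers are (0.09 + 0.08) × 180 ≈ 31 of the 45.

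**Information lost.** Assumptions: compound symmetry, correlation ρ = 0.5, baseline adjusted in both analyses, 75 % complete. The table gives complete-case variance divided by all-available-data variance.

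| When the 25 % leave (assumed) | Post-treatment | 6 months | 12 months |
|---|---|---|---|
| All before post-treatment | 1.00 | 1.00 | 1.00 |
| 8 / 17 / 25 % cumulative | 1.23 | 1.12 | 1.03 |
| All between post-treatment and 6 months | 1.33 | 1.03 | 1.03 |
| All between 6 and 12 months | 1.33 | 1.33 | 1.04 |

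The value 1.33 is 1/0.75. The 1.04 arises as follows:
- Given baseline, the 12-month variance is 1 − ρ² = 0.75.
- Given all three earlier visits, it is 1 − 3ρ²/(1 + 2ρ) = 0.625.
- The all-data variance is proportional to (0.75 − 0.625) + 0.625/0.75 = 0.958, and the complete-case variance to 0.75/0.75 = 1. The ratio is 1/0.958 = 1.04.

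On the confidence-interval scale, 1.33 is a widening of √1.33 = 1.15, and 1.04 of 1.02.

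**Bias (simulation, assumed inputs).** 60 per arm, ρ = 0.6, true effect −0.25 SD, 25 % leaving after the post-treatment visit, contrast at the last visit, 600 repetitions.

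| Drop-out depends on post-treatment distress | Completers | Likelihood, all data |
|---|---|---|
| Equally in both arms | −0.25 (SD 0.212) | −0.24 (SD 0.202) |
| In the treated arm only | −0.38 | −0.25 |

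The likelihood analysis recovers the truth because drop-out was made to depend on an observed score.

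**Controls at 12 months.** If 45 controls are retained and 25 / 50 / 75 / 100 % of them take up a programme (assumed) without a 12-month assessment, about 34 / 22 / 11 / 0 have all four visits.

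**Baseline as outcome.** Compare the group difference in (mean of three post-baseline visits minus baseline) with ANCOVA on that mean, under compound symmetry:
- Variance of the post-baseline mean: v = (1 + 2ρ)/3
- Change: v + 1 − 2ρ
- ANCOVA: v − ρ²

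| ρ | Change | ANCOVA | Ratio |
|---|---|---|---|
| 0.3 | 0.933 | 0.443 | 2.1 |
| 0.5 | 0.667 | 0.417 | 1.6 |
| 0.7 | 0.400 | 0.310 | 1.3 |

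**Binary outcomes.** No arithmetic is needed. Table 3 marks the diagnoses and a yes/no item as primary, and the analysis section offers only MANOVA for comparing arms.

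**The case against.** The strongest reply is that this is a condensed article. Analysis sets, imputation and model terms are commonly left to a statistical analysis plan, and the text neither states a complete-case analysis nor rules out imputation. That stands as far as it goes: excluding incomplete participants is how the named method behaves in its standard form, not a rule the article writes down. But the article does fix the method, and the point is about that choice.

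Other replies also have force. The recruitment target already covers the expected loss. The efficiency figures rest on assumed loss patterns and correlations, and the gain is nil if everyone leaves before post-treatment. With randomised arms, the group-by-time term is a valid test with baseline as an occasion. The covariate list is open-ended.

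Stronger readings are tempting, but the document does not support them:

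- *The analysis is certain to be biased, or is unbiased only if loss is completely at random.* When drop-out depends on distress equally in both arms, completers also give about −0.25. The bias is conditional.
- *The comparison is no longer by randomised group.* Completers stay in their assigned arms; what is lost is the full randomised set.
- *Half of the primary outcome is binary.* Table 3 also marks several scales as primary and labels the diagnostic block as scores. Only suicidal thoughts is expressly yes/no, although the reference to presence of disorder implies binary diagnoses. No fraction can be given.
- *Controls who accept a programme are certainly not seen at 12 months.* The text states that visit only for those who decline, while Tables 1 and 3 list 12 months without separating arms. Selective removal is possible, not established.

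**Conclusion.** The concern holds as a matter of method choice. The only named effectiveness test fits the trial's data poorly, and a better one is available at almost no cost.

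- **Exclusion:** up to about 45 of 180 participants, possibly with further selective removal of controls at 12 months.
- **Precision:** at ρ = 0.5, a complete-case variance penalty of 0 to 33 % at post-treatment and 6 months, and at most about 4 % at 12 months, depending on when people leave.
- **Baseline:** a variance ratio of about 2.1 / 1.6 / 1.3 at ρ = 0.3 / 0.5 / 0.7 under compound symmetry. This is an efficiency loss, not an invalid test.
- **Bias:** a risk that depends on arm-specific, distress-related loss. The −0.38 illustrates one assumed mechanism and is not a forecast.
- **Binary outcomes:** the misfit follows from Table 3 and needs no assumption.

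The change should be made before analysis, but nothing here shows that the trial falls short of its planned 135.

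**What to change.** In Hypothesis and data analysis, replace the MANOVA as the effectiveness analysis:

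- **Scale scores:** a likelihood-based mixed model for repeated measures on all available post-baseline scores of all randomised participants, with arm, visit, arm-by-visit, baseline score as covariate and unstructured covariance. The planned adjustment for pre-injury health and education can stay. Report each active arm versus control with a 95 % CI.
- **Diagnoses and suicidal thoughts:** logistic GEE or mixed logistic models with baseline status as covariate.
- **MANOVA:** at most a sensitivity analysis.

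The text should also say whether controls who take up a programme are assessed at 12 months, since Methods/design and the schedule tables can be read differently. If none are, the 12-month contrast rests on the decliners and on the model.

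The cost is a wording change and slightly more analysis work in standard software, with no new data for the models themselves. The mixed model relies on data being missing at random; GEE needs weighting or imputation to rest on that same assumption. Neither removes bias from loss driven by unobserved distress.

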### Trial organization, registration and ethical aspects

To ensure data integrity the database analyst remains blind to participant allocation details. Data are to be saved in three different locations under tight security with pass-code access only. An additional SPIRIT checklist file shows how the recommendations of a clinical trial protocol have been addressed (see Additional file 1).

## Discussion

This study will allow us to determine whether development of psychological distress and psychological disorders, such as major depressive disorder and post-traumatic stress disorder, can be prevented for motor vehicle crash survivors using brief email-delivered intervention programmes aimed at reducing psychological distress, and improving quality of life, coping and resilience. If the result is positive, and the intervention is acceptable to clients and efficient to administer, it could be implemented by the insurance companies’ regulatory agency as part of standard protocol to all motor vehicle crash survivors. Such a protocol would have the potential to reduce the psychological and economic burdens of motor vehicle crashes with benefits for at-risk people and their families, as well as their employers, with more efficient return to work timeframes, while reducing costs for insurance companies. The results of the study would enable other national and international regulatory agencies to implement a similar preventive intervention strategy.

## Trial status

Two sources of recruitment (national companies with local branches) have been initiated and are actively providing potential participants. The first participant was recruited on 8^th^ August 2015. The expected recruitment period will last until July 2017.

## Abbreviations

ANZCTR, Australian New Zealand Clinical Trials Registry; CBT, cognitive behaviour therapy; SPIRIT, Standard Protocol Items: Recommendations for Interventional Trials
